# Impacts of chest compression cycle length and real-time feedback with a CPRmeter® on chest compression quality in out-of-hospital cardiac arrest: study protocol for a multicenter randomized controlled factorial plan trial

**DOI:** 10.1186/s13063-020-04536-3

**Published:** 2020-07-08

**Keywords:** Cardiac arrest, Cardiopulmonary resuscitation, Chest compression, Quality, Chest compression fraction, No-flow, Guidance

## Abstract

**Background:**

With a survival rate of 6 to 11%, out-of-hospital cardiac arrest (OHCA) remains a healthcare challenge with room for improvement in morbidity and mortality. The guidelines emphasize the highest possible quality of cardiopulmonary resuscitation (CPR) and chest compressions (CC). It is essential to minimize CC interruptions, and therefore increase the chest compression fraction (CCF), as this is an independent factor for survival. Survival is significantly and positively correlated with the suitability of CCF targets, CC frequency, CC depth, and brief predefibrillation pause. CC guidance improves adherence to recommendations and allows closer alignment with the CC objectives. The possibility of improving CCF by lengthening the time between two CC relays and the effect of real-time feedback on the quality of the CC must be investigated.

**Methods:**

Using a 2 × 2 factorial design in a multicenter randomized trial, two hypotheses will be tested simultaneously: (i) a 4-min relay rhythm improves the CCF (reducing the no-flow time) compared to the currently recommended 2-min relay rate, and (ii) a guiding tool improves the quality of CC. Primary outcomes (i) CCF and (ii) correct compression score will be recorded by a real-time feedback device. Five hundred adult nontraumatic OHCAs will be included over 2 years. Patients will be randomized in a 1:1:1:1 distribution receiving advanced CPR as follows: 2-min blind, 2 min with guidance, 4-min blind, or 4 min with guidance. Secondary outcomes are the depth, frequency, and release of CC; length (care, no-flow, and low-flow); rate of return of spontaneous circulation; characteristics of advanced CPR; survival at hospital admission; survival and neurological state on days 1 and 30 (or intensive care discharge); and dosage of neuron-specific enolase on days 1 and 3.

**Discussion:**

This study will contribute to assessing the impact of real-time feedback on CC quality in practical conditions of OHCA resuscitation. It will also provide insight into the feasibility of extending the relay rhythm between two rescuers from the currently recommended 2 to 4 min.

**Trial registration:**

ClinicalTrials.gov, NCT03817892. Registered on 28 January 2019

## Background

Out-of-hospital cardiac arrest (OHCA) remains a challenge for prehospital rescue. With an incidence between 5 and 15 per 10,000 and a survival rate of only 6 to 11% [1–6], there is still room for improvement in care to reduce the morbidity and mortality of these patients. The quality of cardiopulmonary resuscitation (CPR) is at the heart of the last three 5-year recommendations [7–9]. The latest recommendations emphasize the importance of professionals applying the highest possible quality of CPR and chest compressions (CC) [9].

The ratio of the time during which the CC are performed (low-flow) to the total time of resuscitation is referred to as the chest compression fraction (CCF). During CPR, minimizing CC interruptions, and therefore increasing the CCF, is essential, as this is an independent factor of cardiac arrest (CA) survival [10, 11]. CC interruptions are deleterious in at least three ways. First, they are a source of direct stoppage of cerebral and coronary perfusions, potentially altering the neurological prognosis and the probability of return of spontaneous circulation (ROSC) [12]. Second, the quality of the cardiac output generated by CC drops when resuming after an interruption of more than 30 s, the cutoff below which several CC can restore the best cardiac output possible [12, 13]. Third, CC interruptions automatically decrease the CC rate per minute, and difficulty in reaching the upper target of the guidelines’ CC rate has been linked to a significantly higher ratio of ROSC [14]. Reducing these interruptions and improving CC is therefore a major goal of improving CPR. The recommendations state that the CCF must be greater than 60%, and some experts estimate that a CCF of 80% is possible [15, 16].

The outcome of out-of-hospital cardiac arrest (OHCA) is significantly, positively, and independently correlated with the suitability for different CCF targets, CC frequency, CC depth, and brief predefibrillation pause (< 10 s) [17, 18]. Mechanical CC devices have not proven their superiority over manual CC [19], and manual CC remains the gold standard. There is evidence that CC guidance improves adequacy to recommendations and allows closer alignment with the CC frequency, depth, and release objectives [20]. We have demonstrated in simulation that the guidance of the CC delays the deterioration of the overall quality of the CC and its components (frequency, depth, and release) related to fatigue during an extended CC beyond the 2-min CC relay currently recommended [21].

Strategies to better match the recommendations regarding the quality of the CC associated with an improvement in CC should add or even enhance their beneficial effects for the management of CA. Achieving high-quality CPR requires the measurement of the CPR quality (CC and CCF) [22, 23].

This idea of a strategy of support enhanced by the “bundle” of concepts is developing in the literature. Thus, Cheskes et al. [24] describe a “high-quality CPR” such as the combination of a CCF greater than 70% and reaching the objectives in the recommendations for frequency and depth of CC.

The use of tools guiding CC quality still needs to be specified. Indeed, studies on their use in real-life situations are criticized for their methodological qualities and their sample sizes [25]. The use of a real-time guidance tool is proposed as an option in the latest recommendations without being mandatory due to a lack of current evidence [9]. Its use or nonuse does not imply any obvious loss of success for the patients. Evidence of its usefulness therefore remains to be sought.

For this reason, we want to perform an original, randomized, multicenter study to provide some answers to questions about the possibility of improving CCF by lengthening the time between two CC relays and the effect of guidance on the quality of the CC.

The design of the study will also allow us to investigate a possible combined effect of CC guidance and CC relay timing. The duration of a 2-min CC cycle between the two currently recommended relays does not have a solid evidence-based rationale and corresponds to a duration for which the CC effort can a priori be maintained while retaining efficiency [9, 26]. Objective measures have shown that the quality of the CC can be sustained beyond 2 min. Increasing the duration of a CC cycle could reduce the number of CC interruptions and thus improve the CCF.

We therefore formulate two hypotheses that we will test simultaneously using a 2 × 2 factorial design in a multicenter, randomized trial. The first assumption is that a 4-min relay rhythm improves the CCF (reducing the no-flow time) compared to the currently recommended 2-min relay rate. The second hypothesis is that a guiding tool improves the quality of CC.

The CPRmeter^®^ (guidance tool used in this study) will record data on the CC and their quality (depth, frequency, release, CPRmeter^®^ use time, no-flow time, and low-no-flow time) and will provide real-time feedback on CC for the guided group (the other group—blind—will have the screen masked by a screen cap).

Over a period of 2 years, this study will include 500 adult patients presenting with a nontraumatic OHCA for which advanced CPR is undertaken. We hope to improve the knowledge on the optimal rhythm of the CC relay and to validate “in vivo” the value of the guidance attained on manikins. This study should clarify the recommendations with a high level of evidence in this area and thus contribute to improving the prognosis of victims of OHCA.

### Trial objectives

The two main objectives of the 2 × 2 factorial plan are as follows:
Objective 1: To determine whether the CCF gained from the CC relay rhythm of 4 min or 2 min is superiorObjective 2: To determine whether the quality of the CC, as measured by correct compression score (CCS), is superior with guidance or with blinding

## Methods

### Study design and settings

We propose a randomized, multicenter, open-label study using a 2 × 2 factorial design (Protocol CILICA-HS version 4, June 26, 2019) comparing (i) the rhythm of CC relays every 4 min versus every 2 min on the CCF and (ii) the use of real-time guidance of the CC via a guidance tool (CPRmeter^®^) versus no guidance on the quality of the CC (correct compression score). Emergency prehospital services (Service Mobile d’Urgences et de Réanimation) from 12 hospitals in France will participate. The design of the study is summarized in Fig. 1.

**Fig. 1 Fig1:**
[figure not shown]
Study design

The two main objectives of the factorial plan are as follows:
To determine whether a CC relay rhythm of 4 min or 2 min is superior in terms of CCF. CCF corresponds to the fraction of CPR time during which there are CC (low-flow) performed by the out-of-hospital resuscitation team on the OHCA patient.To determine whether the quality of the CC, measured by CCS, is superior with guidance or without guidance (corresponding to good depth, frequency, and release).

The secondary objectives of this study are to determine whether the impact of the guidance on the quality of the CC and on CCF has an isolated or combined effect on the patient’s outcome: ROSC; survival at day 0, day 1, and day 30 (or earlier intensive care exit); the level of brain injury marker neuron-specific enolase (NSE); and neurological outcome at day 30 (or earlier intensive care exit) (CPC score).

### Selection of participants

Potentially eligible subjects are those with an OHCA for whom an out-of-hospital resuscitation team from an investigative center is involved in the first attempt at resuscitation.

### Inclusion criteria

To be eligible, subjects must meet all defined inclusion criteria:
AdultVictim of an OHCAEligible for inclusion procedure in immediate life emergencyAffiliated with the social security system

### Noninclusion criteria

A “noninclusion criterion” refers to a criterion identified or known prior to randomization that prevents inclusion in the study. Subjects meeting any of the following noninclusion criteria will not be eligible to participate in the research:
Not an adultMore than 6 months pregnant or breastfeedingAbsence of indication or contraindication for resuscitation: known incurable disease (advanced neurodegenerative diseases, advanced cancers, …), palliative care in progress, a do-not-resuscitate order from the patient or a decision by the medical team not to resuscitateTraumatic cardiac arrestImpossibility or contraindication to the use of the CC guidance system

### Exclusion criteria

An “exclusion criterion” refers to a secondary finding of a criterion that could not be identified prior to inclusion in the study and that justifies the patient’s exclusion from the study. Subjects meeting any of the following exclusion criteria will not be eligible to participate in the research:
Medical resuscitation started before inclusion by a noninvestigative teamAn automatic CC device was set up before 5 min of CPR in the protocolThe CPRmeter^®^ adhesive could not be fixed on the patient’s torso (large breasts, heavy hair, anatomical abnormality, etc.)Obvious impairment of the CC quality linked to the use of the CPRmeter^®^Discontinuation of CPR before 4 min (excluding ROSC) due to the secondary discovery of the absence of an inclusion criterion or the presence of a noninclusion criterionDiscovery after the arrival of the medical team of an unidentified noninclusion criterion at the time of randomization

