### Trial interventions

CA, matching the eligible criteria, managed by an out-of-hospital resuscitation team can be included according to a procedure of immediate vital emergency (article L1122-1-3 of the Code of Public Health) [27]. The randomization is performed by the out-of-hospital resuscitation team’s doctor during the transportation on the spot to know the randomization arm before the arrival at the place of the intervention. The patient is randomized using the online centralized 24/7 server or the backup sealed opaque “off-grid area” emergency randomization envelopes as described in the “Randomization, allocation” section above.

For all groups, the CPRmeter^®^ CC guidance system was positioned on the patient’s chest with a disposable adhesive. The CPRmeter^®^ is always on for all groups. (1) In the CC guidance situation by the CPRmeter^®^ (group D), rescuers have onscreen real-time visual feedback on the quality of the CC performed and indications of corrections to improve the quality, if necessary. (2) In cases of nonguidance of the CC by the CPRmeter^®^ (blind), a specific screen cap is set up on the screen to hide the feedback in the unguided group (group C). The CPRmeter^®^ is always on to record the CC quality data.

The duration or rhythm of a relay is the time during which a rescuer performs a CC before being relayed by another rescuer. This time is 2 min in group A according to the guidelines in effect and 4 min in group B, which is the experimental group.

The CPR of OHCA is therefore normally undertaken according to the guidelines in effect by the out-of-hospital resuscitation team, except for the relay rhythm in group B, which is 4 min. Due to the 2 × 2 factorial design, four situations are possible (Fig. 1):
CC unguided + relay between 2 rescuers switching at 2 min (C + A)CC unguided + relay between 2 rescuers switching at 4 min (C + B)CC guided + relay between 2 rescuers switching at 2 min (D + A)CC guided + relay between 2 rescuers switching at 4 min (D + B)

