### Safety and potential adverse events

The study implies few changes from OHCA guidelines as real-time feedback is not currently strongly recommended but a possibility, and the time for CPR relay is based on little concrete data [15]. However, feedback tool use has been reported to be safe [20, 34]. In the context of an OHCA, no significant adverse event related to the study is expected. Adverse events can be reported through eCRF, email, and phone calls to the promoter. Serious adverse events will be investigated, and reports will be provided directly to the safety monitoring committee. If they occur, adverse events will be reported in the publication.

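### Patients whose compressions are obviously impaired by the CPRmeter are excluded after randomization, and nothing says they are counted or kept in the safety review

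*Protocol article*

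**What the plan says.** All references are to the protocol article.

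- **Exclusion criteria.** An exclusion criterion is defined as "a secondary finding of a criterion that could not be identified prior to inclusion in the study and that justifies the patient’s exclusion from the" trial. One of those listed is "Obvious impairment of the CC quality linked to the use of the" CPRmeter.
- **Trial interventions.** The doctor randomizes on the way to the scene, "to know the randomization arm before the arrival at the place of the intervention". The device is fixed to the chest in every group and "is always on for all groups"; in the unguided group only the screen is covered. The same section says that a patient later switched to an automated compression device stays in the study, and states which data are kept.
- **Safety and potential adverse events.** The expectation is stated as "In the context of an OHCA, no significant adverse event related to the study is expected". On the channels for reporting, the section says "Adverse events can be reported through eCRF, email, and phone calls to the promoter". For the graver cases it adds "Serious adverse events will be investigated, and reports will be provided directly to the safety monitoring committee". Any adverse events are to appear in the publication.
- **Safety monitoring.** When 250 patients have been included, three independent experts review ROSC and survival (days 0, 1 and 30) by randomized group. The investigator may also request an extra meeting.
- **Statistical analyses.** The exclusions named for the modified intention-to-treat set are unmet inclusion criteria, and death or ROSC at team arrival. Device-linked impairment is not among them.

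**The concern.** An event attributed to the study device is treated as a reason to leave the study, while the safety sections do not mention it. It is the only harm from the device that the article foresees. The Background reports that the outcome of cardiac arrest correlates with meeting compression targets, so obvious impairment of compressions matters to the patient.

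At stake is what the safety committee and the publication can say about the device. If a site takes exclusion from the study at face value, the patient may not appear in the tables the committee sees, and no stated rule requires the case to be counted elsewhere. A report with few or no device problems could then mean that none occurred, or that the affected patients had left the study. A reader could not tell which.

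**Working it through.** The plan gives no figure on this point, so the check is mainly a comparison of sections. The arithmetic only sets a scale.

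**1. When can the criterion be met?** Randomization precedes arrival and the device goes on afterwards, in all groups. Impairment linked to its use can therefore be seen only after both. This is an exclusion after randomization and after exposure.

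**2. What does exclusion do?** The definition speaks of exclusion from the study, not from one analysis. For later use of an automated device, the article expressly keeps the patient and lists the data retained. There is no such sentence for device-linked impairment.

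**3. Do the safety sections pick the case up?** They do not do so by name. The adverse-event section gives reporting channels, sends serious events to the committee and promises publication. It does not say that impaired compressions count as an event. The monitoring section lists ROSC and survival by randomized group; it lists neither exclusions nor compression quality, and does not say whether excluded patients are in the tables.

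**4. Could the by-group tables show the harm anyway?** The contrasts are A vs B (relay length) and C vs D (guidance). The device is worn on both sides of each, so an effect of its physical presence cancels. Only an effect specific to guidance could appear, in C vs D. A direct count of cases is the informative measure.

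**5. Scale.** The total of 500 comes from the section on sample size. Its basis reproduces: n per group = 2 × (1.960 + 1.282)² × 17² / 5² ≈ 243, so 2 × 243 = 486, for which 500 are planned. The rate of device-linked impairment is not given. Assuming 1% to 5%:

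| Assumed rate | Of 500 planned | Of 250 at the safety review |
|---|---|---|
| 1% | 0.01 × 500 = 5 | 0.01 × 250 = 2.5 |
| 2% | 0.02 × 500 = 10 | 0.02 × 250 = 5 |
| 5% | 0.05 × 500 = 25 | 0.05 × 250 = 12.5 |

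These are numbers of patients affected. They would be missing from the review only if exclusion is also taken to end their safety data.

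**The case against.** A reader might infer that the safety data necessarily lose the patients harmed by the device, so that the trial is bound to report no device harm. The article does not say this. The adverse-event route, the referral of serious events to the committee and the promise to publish are not limited to retained patients. A case can be both an exclusion and a reportable event, and the investigator can call an extra committee meeting. The wording that events can be reported most naturally lists channels; it does not clearly make reporting optional. Nor does the monitoring section restrict its tables to patients left after exclusions, and the statistical section does not name this criterion among the modified intention-to-treat exclusions. All of this stands, and it limits the point to what may happen and what is left unstated.

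It can also be said that the full protocol (version 4) is not shown and may define a safety population and device-related events, that device safety is not a trial objective, and that the article rests its safety statement on cited literature. The first is fair: a missing definition alone would be no finding. But the article does state a rule that takes these patients out of the study, and that rule needs a stated consequence for safety reporting.

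A last objection is that keeping these patients in the by-group tables would still not isolate harm from wearing the device. That is correct. The count serves that purpose; keeping the patients makes the tables complete by randomized group and preserves the C vs D comparison of guidance.

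**Conclusion.** The point holds in a limited form. The article excludes patients after randomization and device placement because of an event attributed to the device. Its safety sections neither require that event to be counted nor say that these patients stay in the review. Followed literally, the rule may take them out of the ROSC and survival tables, and the harm may go uncounted.

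It would be too strong to conclude that these cases are certain to be lost, or that the exclusion is the only place where device harm could show. The general adverse-event route remains open, and harm from the guidance itself could differ between C and D.

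The size is unknown. The range of 5 to 25 of 500 patients rests wholly on the assumed 1% to 5%. For the same reason, no upper limit on the device-harm rate should be drawn from a low or zero count: the article plans no such estimate, and the count would depend on how sites read the exclusion.

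**What to change.** - In **Exclusion criteria** and **Safety and potential adverse events**, state that each case of compression impairment linked to the CPRmeter is recorded in the eCRF as a device-related event, whether or not the patient is then excluded.
- Report the number of cases by arm and overall, among patients on whom the device was placed, to the safety committee and in the publication. That denominator leaves out patients in whom the adhesive could not be fixed, who were not exposed.
- In **Safety monitoring**, state that these patients remain in the ROSC and survival tables under their randomized group.

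The cost is one eCRF item, a few sentences of wording and a few more event reports. ROSC and survival are already collected in the study's section of the registry; for these patients that collection has to continue. No clinical rule changes: what the team does when it sees impairment stays as written.

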### Statistical analyses

The main analysis population will be defined as all randomized patients for whom CPR has been engaged, according to a modified intent-to-treat principle. Randomized patients who do not fulfill the inclusion criteria, die, or have a ROSC at prehospital team arrival will be excluded from the main modified intent-to-treat principle analysis. We plan to conduct a pure intent-to-treat analysis in which these excluded patients and patients with missing data will have their outcome imputed by multiple imputation process. This analysis will test the effect of these exclusions on trial outcomes. The statistical analysis plan will follow the recommendations of the tests with a factorial plan described in the CONSORT statement [35], namely, (i) the verification of the absence of interaction between the 2 interventions tested (here on different criteria of judgment) and (ii) a separate analysis by type of multivariate intervention that will systematically include the effect of the untested intervention. Regarding the main criterion of judgment, the average percentage of CCF for comparison of A versus B and the average percentage of CCS for comparison C versus D, the two groups will be compared in terms of superiority of the 4-min group (B) and the guidance group (D) by a multivariate generalized linear regression model including the randomization group as an explanatory variable as well as the other intervention received as a covariable of the model and possibly the interaction of the 2 interventions if it is significant (Student’s test for independent series).

The other criterion (secondary outcomes) will be compared between the groups using the appropriate tests and in an exploratory manner. For example, the qualitative variables will be compared between the groups with the *χ*^2^ test, the quantitative variables by Student’s *t* test, and the survival by the log-rank test.

All confidence intervals of the parameters to be estimated will be established at 5% risk (95% confidence interval). No interim analysis will be performed for primary outcomes (CCF and CCS). The significance level is set at 0.05. The analysis will be performed in SAS software v9.4 (SAS Institute NC, Cary).

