### Determination of sample size

We estimated the calculation of the number of subjects required in this trial using a factorial design for the comparison of 2 min versus 4 min (A vs B) on the average percentage of CCS.

With an average CCF of 70% [36] in the control group (group A, 2 min) and a 5% improvement in the experimental group (group B, 4 min), a power of 90%, a two-tailed alpha risk of 5% bilateral, and a standard deviation of ± 17%, 243 subjects per group are required to compare the effect of 2 min versus 4 min (A vs B) on the average percentage of CCF.

Regarding the guiding hypothesis, with a difference of 15% in the CCS between the guided group (D) and the blinded group (C), a standard deviation of ± 36% (12), alpha 5%, and beta 10%, the number of subjects needed is lower (122 per group).

We plan to include 500 patients according to the sample size needed for hypothesis A vs B (243 per group), which is higher than that needed for hypothesis C vs D (122 per group).

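### The exclusion criteria and the analysis section define different primary analysis sets, and some exclusions made after open-label randomisation can be influenced by arm and by compression quality

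*Protocol article*

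**What the plan says.** Two sections of the protocol article decide who is analysed.

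- **Exclusion criteria** lists findings made after inclusion that take the patient out of the study. Three of them can arise only once the team is treating the patient: an automatic compression device set up before 5 min of protocol CPR, an adhesive that cannot be fixed to the chest, and "Obvious impairment of the CC quality linked to the use of the" CPRmeter. The last has no threshold, and nobody is named to judge it.
- **Statistical analyses** defines the main set as "all randomized patients for whom CPR has been engaged, according to a modified intent-to-treat principle". It removes only patients who do not meet the inclusion criteria or who are dead or have a ROSC when the team arrives. It adds a pure intent-to-treat analysis in which those excluded patients, and patients with missing data, have their outcome imputed.

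Three other statements bear on how the exclusions would work in practice. Under Trial interventions, the doctor randomises on the way to the scene, "to know the randomization arm before the arrival at the place of the intervention". Under Blinding, providers are not blinded. Under Trial interventions again, the CPRmeter is fixed and switched on in all four groups, but its screen is capped in group C and visible in group D.

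**The concern.** A patient who receives CPR and then meets one of the three criteria is excluded by one section and retained by the other. Whoever builds the dataset must choose between them, and the choice decides who enters both primary comparisons.

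The choice matters because these exclusions follow an open allocation. A team that knows the arm, and in group D watches a quality display that group C cannot see, decides without a threshold whether the device is impairing compressions. Compression quality is what the CCS measures. The moment at which an automatic device is chosen is also a team decision, taken while the assigned relay rhythm is running. If such decisions differ between arms and are related to the outcome, the retained patients are no longer a randomised comparison.

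**Working it through.** **1. The two rules side by side, for a randomised patient with CPR engaged**

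| Event during care | Exclusion criteria | Main set in Statistical analyses |
|---|---|---|
| Automatic device before 5 min of protocol CPR | out | in |
| Adhesive cannot be fixed | out | in |
| Obvious quality impairment linked to the CPRmeter | out | in |

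None of the three is among the inclusion criteria (adult, OHCA, eligible for the emergency inclusion procedure, social security affiliation), and none is death or ROSC at arrival. The conflict is on the page.

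**2. The plan's own figures**

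Inputs from Determination of sample size: "a power of 90%, a two-tailed alpha risk of 5% bilateral"; for CCF, "a 5% improvement in the experimental group (group B, 4 min") and "a standard deviation of ± 17"%; for CCS, "with a difference of 15% in the CCS between the guided group (D) and the blinded group (C") and an SD of 36%. The formula is n per group = 2 × (1.960 + 1.282)² × SD² / difference².

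- CCF: 2 × 10.507 × 17² / 5² = 242.9, so 243, as stated.
- CCS: 2 × 10.507 × 36² / 15² = 121.05, so 122, as stated.

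The sample size arithmetic is sound. The point concerns who is analysed.

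**3. Worst case for CCS**

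Assumptions not given in the document: mean CCS of 40, 50 or 60; a beta-shaped score on 0 to 100 with SD 36; exclusions in one arm only; and removal of exactly the lowest share p. With mean m on a 0 to 1 scale, k = m(1 − m)/0.36² − 1, a = mk and b = (1 − m)k. For m = 0.4 this gives k = 0.852, a = 0.341, b = 0.511. The shift is the mean above the p-th quantile minus m. The mathematical ceiling, reached if everyone removed scored zero, is m × p/(1 − p).

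| Share removed | Shift, mean 40 / 50 / 60 | Ceiling | Share of the 15-point target |
|---|---|---|---|
| 5% | 2.1 / 2.6 / 3.1 | 2.1 / 2.6 / 3.2 | 14% to 21% |
| 10% | 4.4 / 5.5 / 6.5 | 4.4 / 5.6 / 6.7 | 30% to 43% |

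With 250 per margin (500/2), no true effect and 5% removed, the standard error is about 3.2 points. The two-sided type I error then becomes about 10% to 17% instead of 5%.

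**4. CCF**

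No exclusion criterion acts on CCF itself, so any effect runs through a correlation ρ that the document does not give. Using a normal score, shift = ρ × 17 × φ(z)/(1 − p). At p = 5% in one arm this is ρ × 17 × 0.1031/0.95 = 1.85ρ. With ρ = 0.25 it is 0.46 points, or 9% of the 5-point target.

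**5. If exclusions are balanced and unrelated to outcome**

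There is then no bias, only lost power for CCF. The plan states that "243 subjects per group are required to compare the effect of 2 min versus 4 min (A vs B"), so 500 leaves 500 − 486 = 14 patients (2.8%) for all losses. CCF power is 90.8% at 250 per group, 90.0% at 243 and 87.7% at 225 (a 10% loss).

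**The case against.** A reader might infer that the exclusions depend on arm, that they do bias both primary comparisons, and that the bias favours guidance. The documents do not support that reading, for these reasons.

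- No criterion names an arm, and all apply to all four groups. Only their application can be influenced by allocation.
- The quality criterion covers impairment caused by the device, not poor compressions in general, and the device is on the chest in every group. Overlap with the CCS arises through loose application of a criterion that has no threshold.
- The direction is open. If guidance works, poor compressions are commoner in group C; exclusions there would raise its mean and shrink the difference. The visible display in group D could push the other way.
- For CCF the main route is an early automatic device. Before 5 min a 4-min arm has had at most one relay, and the document does not say why or how often devices are set up so early.
- The figures in the table for CCS are practically the ceiling, for perfect selection in one arm only.

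There is also a planned safeguard: the pure intent-to-treat analysis is meant to test the effect of exclusions. It helps, but only partly. It is not the main analysis. Its wording refers back to the exclusions listed in Statistical analyses and does not clearly reach those under Exclusion criteria, although some of these patients might enter as missing data. Imputing from retained patients does not undo selection on poor quality.

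Finally, failure to meet the inclusion criteria could be read loosely to cover the noninclusion criterion on impossibility of using the guidance system, and so adhesive failure. That would still leave an early automatic device outside the list, and device-linked impairment at best uncertain.

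**Conclusion.** The point holds as a contradiction between two sections, together with a risk of bias. The primary analysis set is defined in two incompatible ways. Under one of them, patients leave after open-label randomisation for reasons that allocation can influence and that, for the quality criterion, overlap a primary outcome. The risk is direct for the CCS comparison and less direct for the CCF comparison.

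Neither direction nor size can be derived from the document, which gives no exclusion rates and no mean CCS. The 2.1 to 3.1 points for CCS is an upper bound for a 5% loss confined to one arm, not an estimate. Balanced exclusions unrelated to outcome would cause no bias. Since the set decides who enters both primary comparisons, the sections must be reconciled before outcome data by arm are seen.

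**What to change.** State one primary set, in the same words, in both sections: all randomised patients for whom CPR was engaged, analysed as randomised. Allow exclusion only for facts that precede the intervention and are ascertained independently of arm. Then:

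1. Keep patients with device-linked impairment or an early automatic device, using the compression data recorded up to that event. Concomitant care and interventions already applies this rule when the automatic device comes after 5 min.
2. Where no usable recording exists, for example after adhesive failure, treat the outcome as missing and name these patients explicitly in the planned multiple imputation.
3. Report every post-randomisation exclusion by arm and reason.

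This changes the analysis set only, not clinical management. It costs a rewording of two sections and one table; the CPRmeter is on in all groups and records automatically. The small downside is that some short recordings enter the CCF and CCS analyses, although both outcomes are defined over the duration of CPR. A prespecified sensitivity analysis on recording length can address that.
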